**Division:** Worldwide Development

**Retention Category:** GRS019

**Information Type:** Clinical Pharmacology Protocol

| **Title:** | Effect of Metformin on gut peptides , bile acids and lipid profiles in Type 2 Diabetics | |
| --- | --- | --- |
| **Compound Number:** | | None |
| **Effective Date:** | | 07-JUN-2010 |

**Description**: Metformin is a biguanide that is marketed as an oral anti-diabetic drug. Metformin treatment in concert with diet and exercise is the consensus first-line treatment for type 2 diabetes mellitus (T2DM), and therefore it will likely be an adjunct therapy for all assets in development by GSK for the treatment of T2DM. Metformin has potent effects in lowering circulating glucose concentrations, and it is believed to have additional benefits in improving macrovascular outcomes, fatty liver disease and polycystic ovarian syndrome. Its use in a significant proportion of T2DM subjects is limited by contraindications of heart failure and renal insufficiency or gastrointestinal side effects. The mechanisms underlying the glucose-lowering effect and adverse event profile of metformin are not well understood. Whilst activation of AMP kinase may be important for therapeutic effect, changes in incretin secretion and bile acid excretion have been described, but not consistently linked to its therapeutic effect or AE profile. The aim of this study is to recruit T2DM patients on prescribed metformin monotherapy to further investigate how the glucose effects are related to the alterations in bile acid absorption, incretin and lipid profiles by studying these parameters on and off the drug. This will be done in combination with frequent capillary blood glucose monitoring to ensure patient safety. This study will facilitate the development of a pharmacodynamic model that can be used by clinical teams developing non-absorbable NCEs such as iBAT inhibitors.

**Subject:** Diabetes, Metformin, Bile Acid, Incretin, Lipid Profile

| ALT | Alanine aminotransferase (SGPT) |
| AMPK | AMP-activated protein kinase |
| ANOVA | Analysis of Variance |
| AST | Aspartate aminotransferase (SGOT) |
| AUC | Area under concentration-time curve |
| AUC(0-∞) | Area under the concentration-time curve from time zero (pre-dose) extrapolated to infinite time |
| %AUCex | Percentage of AUC(0-∞) obtained by extrapolation |
| AUC(0-x) | Area under the concentration-time curve from zero (pre-dose) to some fixed nominal time x |
| AUC(0-t) | Area under the concentration-time curve from time zero (pre-dose) to last time of quantifiable concentration within a subject across all treatments |
| AUC(0-τ) | Area under the concentration-time curve over the dosing interval |
| β-HCG | Beta-Human Chorionic Gonadotropin |
| BA | Bioavailability |
| BE | Bioequivalence |
| BMI | Body mass index |
| BP | Blood pressure |
| BPM | Beat Per Minute |
| BQL | Below the quantification limit |
| BUN | Blood urea nitrogen |
| CBC | Complete blood count |
| CI | Confidence Interval |
| CIB | Clinical Investigator’s Brochure |
| CLr | Renal clearance |
| CL | Systemic clearance of parent drug |
| CL/F | Apparent clearance following oral dosing |
| Cmax | Maximum observed concentration |
| Cmin | Minimum observed concentration |
| Cτ | Pre-dose (trough) concentration at the end of the dosing interval |
| Ct | Last observed quantifiable concentration |
| CDMP | Clinical Document Management and Publishing |
| CO_2_ | Carbon dioxide |
| CPDS | Clinical Pharmacology Data Sciences |
| CPK | Creatine phosphokinase |
| CPMS | Clinical Pharmacokinetics Modelling & Simulation |
| CPSR | Clinical Pharmacology Study Report |
| CP-RAP | Clinical Pharmacology Reporting and Analysis Plan |
| CRF | Case Report Form |
| CRO | Contract Research Organization |
| CRU | Clinical Research Unit |
| CSSO | Clinical Science and Study Operations |
| CV | Coefficient of variance |
| DB | Discovery Biometrics |
| DBP | Diastolic blood pressure |
| DDS | Drug Development Sciences |
| DILI | Drug Induced Liver Injury |
| DMPK | Drug Metabolism and Pharmacokinetics |
| DNA | Deoxyribonucleic acid |
| EDC | Electronic data capture |
| EISR | Expedited Investigator Safety Report |
| Fabs | Absolute bioavailability of drug determined following extravascular and intravascular dosing |
| FDA | Food and Drug Administration |
| Frel | Relative bioavailability of drug determined between two formulations of the same drug following similar or different extravascular route of administration |
| FSH | Follicle Stimulating Hormone |
| FTIH | First time in humans |
| GCP | Good Clinical Practice |
| GCSP | Global Clinical Safety and Pharmacovigilence |
| GGT | Gamma glutamyltransferase |
| GLP | Good Laboratory Practice |
| GLS | Geometric Least-Squares |
| GSK | GlaxoSmithKline |
| HBsAg | Hepatitis B surface antigen |
| hCG | Human chorionic gonadotropin |
| HIV | Human Immunodeficiency Virus |
| h/hr | Hour(s) |
| HR | Heart rate |
| HWE | Hardy-Weinberg Equilibrium |
| IB | Investigator’s Brochure |
| ICH | International Conference on Harmonization of Technical Requirements for Registration of Pharmaceuticals for Human Use |
| IDMC | Independent Data Monitoring Committee |
| IDSL | Integrated Data Standards Library |
| IEC | Independent Ethics Committee |
| IND | Investigational New Drug |
| IP | Investigational Product |
| IRB | Institutional Review Board |
| IU | International Unit |
| IV | Intravenous |
| Kg | Kilogram |
| λz | Terminal phase rate constant |
| L | Liter |
| LFTs | Liver function tests |
| Ln | Naperian (natural) logarithm |
| LOQ | Limit of quantification |
| LLQ | Lower limit of quantification |
| µg | Microgram |
| µL | Microliter |
| MAT | Mean absorption time |
| MCH | Mean corpuscular hemoglobin |
| MCHC | Mean corpuscular hemoglobin concentration |
| MCV | Mean corpuscular volume |
| MedDRA | Medical Dictionary for Regulatory Activities |
| Mg | Milligrams |
| mL | Milliliter |
| MRT | Mean residence time |
| MSDS | Material Safety Data Sheet |
| Msec | Milliseconds |
| NCE | New Chemical Entity |
| NQ | Non-quantifiable concentration measured as below LLQ |
| PD | Pharmacodynamic |
| PGx | Pharmacogenetics |
| PK | Pharmacokinetic |
| PSRI | Periodic Safety Reports for Investigators |
| QC | Quality control |
| QD | Once daily |
| QTcB | QT duration corrected for heart rate by Bazett’s formula |
| QTcF | QT duration corrected for heart rate by Fridericia’s formula |
| RAP | Reporting and Analysis Plan |
| RBA | Relative Bioavailability |
| RBC | Red blood cells |
| RNA | Ribonucleic acid |
| SAE | Serious adverse event(s) |
| SAS | Statistical Analysis Software |
| SD | Standard deviation |
| SGOT | Serum glutamic-oxaloacetic transaminase |
| SGPT | Serum glutamic pyruvic transaminase |
| SOP | Standard Operating Procedure |
| SPM | Study Procedures Manual |
| SUSAR | Suspected, Unexpected, Serious Adverse drug Reaction |
| T2DM | Type 2 Diabetes Mellitus |
| T | Time of last observed quantifiable concentration |
| t½ | Terminal phase half-life |
| Τ | Dosing interval |
| Tlag | Lag time before observation of drug concentrations in sampled matrix |
| Tlast | Time of last quantifiable concentration |
| Tmax | Time of occurrence of Cmax |
| ULN | Upper limit of normal |
| UK | United Kingdom |
| WBC | White blood cells |

Trademark Information

| **Trademarks of the GlaxoSmithKline group of companies** |  | **Trademarks not owned by the GlaxoSmithKline group of companies** |
| --- | --- | --- |
|  |  | Metformin |
|  |  | Entero-Test |
|  |  | WinNonlin |

# Introduction

## Background

The metabolic syndrome and its pathological sequela, type 2 diabetes mellitus (T2DM), have become major health problems across the world. The biguanide metformin is widely used as a first-line therapy for the treatment of T2DM based on the results from outcome studies such as the UKPDS [UKPDS, 1998]. In addition, the drug has recently been proposed for the treatment and/or prevention of fatty liver diseases and polycystic ovary syndrome [Glueck, 2003]. Metformin ameliorates hyperglycaemia by reducing gastrointestinal glucose absorption and hepatic glucose production and by improving glucose utilisation [Natali, 2006]. The molecular mechanisms underlying the action of metformin appear to be related to the phosphorylation of the energy sensor AMP-activated protein kinase (AMPK), which suppresses glucagon-stimulated glucose production and causes an increase in glucose uptake in muscle and in hepatic cells [Correia, 2008; Kirpichnikov, 2002]. However the pharmacology of metformin is still not fully elucidated because activation of AMPK does not explain all its metabolic effects. Indeed there have been inconsistent reports that metformin increases active GLP-1 [Mannucci, 2004], perhaps by inhibiting DPP-IV, a dipeptidyl peptidase that cleaves a number of bioactive peptides including glucose-dependent insulinotropic peptide (GIP), glucagon-like peptide (GLP-1) and peptide-tyrosine-tyrosine (PYY) secreted from enteroendocrine K and L cells in the upper and lower gut, respectively. There are also data indicating that metformin increases bile acid content of faeces [Carter, 2003] and this may result in activation of the TGR-5 receptor on enteroendocrine cells [UKPDS, 1998] and perhaps also may contribute to the gastrointestinal intolerance that is occasionally experienced by T2DM patients taking this drug.

## Study Rationale

As metformin has become first-line therapy for T2DM patients in many countries, it is important to ensure early-on in development that novel anti-diabetic NCEs work well as add-ons to this drug. Furthermore, the broad spectrum of effects of metformin that may be related to its glucose-lowering action offers the opportunity to use this drug as an investigative tool to explore the relationship between the various pharmacodynamic endpoints. The Entero-Endocrine DPU (EE-DPU) has a strategy to develop agents that act locally in the gastrointestinal tract to control blood glucose, with little or no systemic exposure. In this situation, reliable PD endpoints are essential to monitor pharmacology because systemic drug concentration measurements would not be available to track how a drug target is being activated or inhibited. In this situation, reliable PD endpoints are essential because systemic PK measurements are not available to track how a NCE target is being activated or inhibited. Therefore, a clearer understanding of metformin’s mechanism of action as it relates to glycaemic control, lipid metabolism, bile acid excretion and gastrointestinal adverse effects will enable the EnteroEndocrine (EE) project teams to design more efficient studies for the evaluation of non-absorbable NCEs targeted to receptors that are accessible from the gut lumen, including the ileal bile acid transport inhibitor.

Because of the complexity of metformin kinetics within the gut, it is proposed to follow the rise and fall of fasting blood glucose during metformin washout and re-introduction, respectively, to determine the two appropriate timepoints for more detailed investigation. As a result, subjects will be studied on 4 occasions:

1. Whilst on their usual stable dose of metformin (baseline state),
2. 7 days after stopping metformin to replicate the washout paradigm frequently used in early phase T2DM studies in GSK
3. When fasting capillary glucose has increased by 25% from the pre-metformin washout level or two weeks from the start of the wash-out period.
4. After metformin is re-introduced, when fasting capillary glucose has returned to the pre-metformin washout level (baseline state established at screening )

## Summary of Risk Management

This study will entail the withdrawal and re-introduction of metformin under closely supervised conditions. The withdrawal of metformin will be for a maximum period up to three weeks and the glucose increases projected are not expected to result in significant long-term risk for the subjects.

If subjects do not already test blood glucose at home, a glucometer, instructions on its use, and testing strips will be provided to them for capillary blood glucose (CBG) monitoring during withdrawal and reinstatement of metformin. They will be instructed to test their blood glucose twice a day, fasting before breakfast and before dinner, and at any time they are concerned that blood glucose may have risen excessively. A written diary card will be kept by each subject for recording CBG values, beginning approximately 7 days before discontinuation of metformin after baseline assessments are completed during visit 1.

Fasting CBG values >15mM or < 3.5mM must be reported to the site at once. If fasting CBG are >15mM or < 3.5 mM on any two consecutive days during the wash-out period, the subject will be discontinued and the usual dose of metformin will be reinstated, if appropriate

Subjects are required to call the study centre while not in the unit or to alert site staff while in the clinical unit:

- When they have CBG values that are >15mM
- When they have CBG values that are <3.5mM
- When they have any concerns relating to their CBG levels
- When they have rapid, unexplained changes in their blood glucose levels

Study staff will attempt to contact the subjects daily to check on the CBG values and to record any adverse events whilst the subject is at home.

Subjects will be encouraged to keep their usual lifestyle in term of diet and exercise for all duration of the study.

The Entero-Test device is simple, safe device for the collection of duodenal bile. It is well tolerated, although some subjects may feel slight nausea on removal. Some blood may be seen on the string when removed. This occurs if the string “nicks” the oesophagus on removal, this is very minor trauma that heals rapidly and is not a cause for concern.

# OBJECTIVE(S)

## Primary

To investigate the relationship between the glucose lowering action of metformin and:

- Faecal and serum bile acid concentrations
- Enteroendocrine peptide profiles including but not limited to incretins and PYY
- Lipid metabolism including but not limited to fasting lipids and prandial TGs

## Secondary

- To provide a relative estimate of the composition of bile acids in bile sampled using the EnteroTest string
- To measure sparse metformin profiles on the days when the PD endpoints are measured

## Exploratory Objective

In the event of erroneous changes in glucose profiles observed subsequent to changes in a subjects routine metformin dosing, we may screen the subject’s genome for alleles known to alter responses to metformin such as OCT1. This analysis will be performed using samples obtained under the PGx consent.

# ENDPOINT(S)

## Primary

During metformin wash out and when treatment reinstated, pharmacodynamic endpoints will include the following as data permit:

- 24h profiles of blood glucose and insulin
- Faecal and serum bile acid profiles
- Enteroendocrine peptide profiling including but not limited to tGLP-1, tGIP, and tPYY
- Serum lipid analysis including but not limited to fasting HDL and LDL cholesterol, fasting and prandial TGs, ApoA1, ApoB and ApoE

## Secondary

- Relative bile acid composition as determined by EnteroTest bile string sampling of duodenal bile.
- Sparse metformin PK profiles will be determined from plasma samples

## Exploratory

- Genetic testing for variants of metformin influx into and efflux from hepatocytes

# INVESTIGATIONAL PLAN

## Study Design/Schematic

## Discussion of Design

Because of the complexity of the entero-cellular kinetics of metformin, the period of time for investigation after metformin discontinuation or restart will be determined by monitoring the changes in fasting glucose. Thus, gastrointestinal and related markers are measured at the most informative times when there are visible changes in glucose. Subjects will be contacted daily by telephone by site staff from 7 days before Visit 1 until discharged following Visit 4.

**Visit 1** - At the first clinical unit admission (Visit 1) full PD profiles will be obtained whilst subjects are taking their usual dose of metformin.

**Visit 2 -** The first PD profiling during the metformin washout phase will be conducted 7 days after the first baseline visit to simulate the situation in early phase studies when T2DM subjects are washed off metformin for a fixed period of time.

**Visit 3 -** During the metformin washout, the site staff will continue to monitor patient progress daily and will schedule the subject for admission into the clinical unit for PD profiling (Visit 3) when the fasting CBG has increased by 25% or approximately 3 weeks has passed, whichever is sooner. If the average fasting CBG increases by the required amount within 7 days following Visit 1, then visit 3 will be eliminated and the subject will be asked to restart metformin after visit 2 is completed.

**Visit 4-** In the metformin re-start phase of the study, site staff will inform the subject when the fasting CBG has returned to the baseline level (determined at screening) and the subject will be scheduled for admission into the clinical unit for PD profiling. If the subject’s CBG has not returned to baseline level (approximate) within approximately 14-21 days, this visit will be scheduled once the subject has achieved clinically acceptable glycaemic control, in the opinion of the principal investigator.

The study will enrol approximately 16 subjects to ensure that12 fully evaluable T2DM patients complete the study. The study will consist of a screening visit and, 4 in-house study visits and a follow up visit, taking approximately 12 weeks to complete the study.

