Upon discharge from Visit 3, subjects will resume their usual prescribed dose of metformin treatment and return to the unit for study Visit 4 once their fasting CBG returns to their baseline level (approximate) or achieve clinically acceptable gycaemic control, as determined by the principal investigator. Pharmacodynamic samples, faecal and bile acid collections will be repeated according to the schedule detailed in Section 4.4.

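### Visit 4 is timed by glycaemic state with no minimum time since metformin restart, so subjects whose glucose rose little may be profiled after very short re-exposure

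*Protocol*

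**What the plan says.** Three sections of the protocol define Visit 4, each by glycaemic state.

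- Study Rationale: "After metformin is re-introduced, when fasting capillary glucose has returned to the pre-metformin washout level".
- Discussion of Design: "site staff will inform the subject when the fasting CBG has returned to the baseline level (determined at screening) and the subject will be scheduled". A fallback there covers slow returners: "not returned to baseline level (approximate) within approximately 14-21 days, this visit will be scheduled once the subject has achieved clinically acceptable glycaemic control". The principal investigator judges whether that is so.
- Study Visits: subjects "return to the unit for study Visit 4 once their fasting CBG returns to their baseline level (approximate", with the bracket closing and the investigator-judged alternative following as a plain alternative, without the 14-21 day wait.

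None of the three, nor the Time and Events Table, gives a minimum number of days back on metformin. None says whether one reading or an average decides that CBG has returned.

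Two other rules bear on this. Visit 3 takes place "when the fasting CBG has increased by 25% or approximately 3 weeks has passed, whichever is sooner" according to Discussion of Design, and Study Visits also uses about three weeks. Study Rationale instead has the limb "or two weeks from the start of the wash-out period". On restart, Study Visits says "Upon discharge from Visit 3, subjects will resume their usual prescribed dose of metformin treatment".

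**The concern.** The elapsed-time limb of Visit 3 exists because some subjects may not reach a 25% rise. If such a subject's fasting glucose has stayed at, or within daily noise of, the pre-washout level, the Visit 4 condition is already met on the day metformin resumes. The plan provides for subjects who return too slowly, but not for those who never moved away.

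Discussion of Design justifies glucose-triggered timing on the ground that markers should be sampled when glucose is visibly changing. For a subject with no rise there is no such change, and the trigger carries no information about re-exposure.

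Visit 4 is the only profile after re-introduction. The study has one regimen and no parallel control (Treatment Assignment), so this visit is its only within-subject view of whether washout changes go back when the drug returns. The reinstated-treatment phase is also named in the primary endpoints. If time on drug is shortest in those whose glucose rose least, Visit 4 values mix unequal exposures in a way tied to the glucose response, which the primary objective sets out to relate to the markers.

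**Working it through.** The plan gives no figure to reproduce here, so the check is of the rule as written.

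**Inputs from the protocol.** Baseline is the mean of about 7 fasting readings before Visit 1 (Screening visit, Study Visits). There is one fasting reading a day, reviewed daily by telephone. Restart is at discharge from Visit 3.

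**Assumptions not in the protocol.** Day-to-day CV of fasting CBG is 8-15%. Readings are independent and Normal, with SD proportional to the level. The true rise at restart is r = 0, 5, 10 or 25%. In the first calculation metformin has had no effect yet.

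**3-day mean rule.** With baseline scaled to 1, the baseline mean has variance CV²/7 and the mean of three later readings has variance CV²(1+r)²/3. So

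P(3-day mean ≤ baseline) = Φ( −r / [CV·√(1/7 + (1+r)²/3)] ).

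- r = 0: Φ(0) = 0.50 at any CV.
- r = 0.05: the root is √(0.1429 + 0.3675) = 0.714. CV 8%: Φ(−0.875) = 0.19. CV 15%: Φ(−0.467) = 0.32.
- r = 0.10: the root is √(0.1429 + 0.4033) = 0.739. CV 8%: Φ(−1.69) = 0.045. CV 15%: Φ(−0.902) = 0.18.
- r = 0.25: the root is √(0.1429 + 0.5208) = 0.815. CV 8%: below 0.001. CV 15%: Φ(−2.05) = 0.02.

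**Single-reading rule.** The three readings share one estimated baseline, so average over it:

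P(at least one of 3 ≤ baseline) = 1 − ∫ [1 − Φ((CV·z/√7 − r)/(CV(1+r)))]³ φ(z) dz.

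For r = 0 this is 0.84 at any CV. It would be 1 − 0.5³ = 0.875 if the baseline were known exactly.

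| True rise at restart | Single reading, CV 8% to 15% | 3-day mean, CV 8% to 15% |
|---|---|---|
| 0% | 84% | 50% |
| 5% | 61% to 73% | 19% to 32% |
| 10% | 35% to 61% | 5% to 18% |
| 25% | 2% to 27% | 0% to 2% |

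**Sensitivity: the drug starts to act.** In a simulation of 200,000 subjects per scenario, the rise decays with an assumed 4-day half-life and CV is 7-15%. On the single-reading rule, the chance of a trigger by day 2 is 73% (no rise), 51-63% (5%), 30-53% (10%) and 3-28% (25%). The median trigger day is 2 for a rise of 0-5%, 2-4 for 10% and 4-8 for 25%. If approximate baseline is read as within 5%, the day-2 chances are 84-92%, 76-79% and 58-66% for rises of 0, 5 and 10%. With a 3-day mean the earliest trigger is day 3, with chances of 50%, 23-37% and 8-26%.

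Under every reading, the smaller the washout rise, the sooner Visit 4 can be called.

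**The case against.** Glucose-triggered timing is deliberate and explained: gut kinetics are complex, and the primary objective relates markers to the glucose-lowering action. Visit 2's fixed 7 days has its own purpose, to imitate the washout used in early-phase studies, so the absence of an on-drug mirror is not an inconsistency. That stands, and it means nothing in the protocol supports 7 days as the re-treatment interval.

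The rule is also not purely a return to baseline. A reader might infer that it is, but an investigator-judged alternative exists. It does not help here, because it is itself glycaemic, sets no lower limit and, in Study Visits, could bring the visit forward.

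A single reading is the least favourable interpretation. Neighbouring rules speak of average or mean CBG, and scheduling an admission takes time. A reader might infer that subjects will be profiled after a day or two. The protocol states no such figure, and under a 3-day mean the trigger cannot fall before day 3. The rule works reasonably for a subject who did rise by 25%.

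Metformin is measured on profiling days and sample times are recorded, so days since restart can be derived. That allows reporting afterwards but does not prevent an early profile; a plasma level shows that drug is present, not how long it has been back.

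Finally, the lead contrast is Visits 1 to 3 and no hypothesis is formally tested. A reader might infer that failure to reverse at Visit 4 will be taken as evidence against a metformin effect, but no section says so.

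**Conclusion.** The gap is real and moderate in weight. As written, the Visit 4 rule can classify a barely re-exposed subject as re-treated, because it has no minimum time since restart and a subject can arrive at restart without a glucose rise. For a subject with no rise, the chance of qualifying within three daily readings is about 84% on a single reading and 50% on a 3-day mean. It falls as the rise grows and is small at 25% except with noisy readings judged singly. These figures rest on an assumed CV of 8-15%, independent readings and no drug effect in the first days. The direction is the same when a drug effect is allowed.

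The share of the roughly 12 evaluable subjects who would reach the time cap with little rise cannot be obtained from the protocol, so the effect on Visit 4 means or correlations is not quantified. A reader might infer that the main result is compromised. It is not: the Visit 1 to Visit 3 differences do not use Visit 4.

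**What to change.** 1. Reconcile Study Rationale, Discussion of Design and Study Visits on how return to baseline is judged, including whether one reading or an average counts and what approximate means. A multi-day mean, for example, would match the 7-day mean baseline. The same sections should be reconciled on when the investigator-judged alternative applies and on the two-week versus three-week limit for Visit 3.
2. Add a minimum interval since restart before the Visit 4 profile, chosen and justified by the sponsor. It governs the day of the assessment only, not treatment.
3. Report Visit 4 results with days since restart, and with whether Visit 3 was reached by glucose rise or by the time cap.

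The cost is a few sentences of protocol text, and some subjects attend a few days later. A minimum interval limits the tie between time on drug and glucose response but does not remove it, because time beyond the minimum still depends on glucose. The third step is therefore needed as well.
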